## Abstract

**Background:**

Young women in sub-Saharan Africa remain at the epicentre of the HIV epidemic, with surveillance data indicating persistent high levels of HIV incidence. In South Africa, adolescent girls and young women (AGYW) account for a quarter of all new HIV infections. Determined, Resilient, Empowered, AIDS-free, Mentored and Safe (DREAMS) is a strategy introduced by the United States President’s Emergency Plan for AIDS Relief (PEPFAR) aimed at reducing HIV incidence among AGYW in 10 countries in sub-Saharan Africa by 25% in the programme’s first year, and by 40% in the second year. This study will assess the change in HIV incidence and reduction in risk associated behaviours that can be attributed to the DREAMS initiative in South Africa, using a population-based cross-sectional survey.

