### Study objectives

The primary objective of this study is:
Measure the change in HIV-1 incidence following implementation of the DREAMS suite of interventions within a ‘real world, non-trial setting’.

The secondary objectives are to:
Measure HIV prevalence, and proportion of HIV positive AGYW on ART and ART naïve with detectable and undetectable HIV-1 Ribonucleic Acid (RNA) viral load.Measure prevalence of pregnancies and sexually transmitted infections (STIs) including Hepatitis B virus (HBV), Herpes simplex virus type 2 (HSV-2), syphilis, human papillomavirus (HPV*), Chlamydia trachomatis*, *Neisseriae gonorrhoea*, *Trichomonas vaginalis* and *Mycloplasma genitalium.*Measure risky sexual behaviour, specifically, the number of past year sexual partners, condom use, and age-disparate and concurrent partnering.Measure the prevalence of intimate partner violence.Measure performance on selected academic milestones (e.g. academic progress, school completion rates).Measure the economic empowerment of AGYW, socio-economic status of their family and selected parent/guardian/caregiver indicators.To measure the exposure to the DREAMS programme including condom promotion and provision (male and female); HIV testing services (HTS) and linkage to care; GBV prevention and post violence care and support; comprehensive sexual reproductive health rights (SRHR) services; social asset building interventions; school-based HIV and violence prevention; community mobilization and norms change; parenting/caregiver programmes.

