### Study design

This study is a single cross-sectional survey targeting 18,500 AGYW, to be conducted in 2017/2018 in four selected districts in South Africa. AGYW between 12 and 24 years will be selected using a stratified cluster-based sampling approach, with districts representing strata and the cluster or primary sampling unit being the small area layers (SALs). SALs were created by merging adjacent Enumeration Areas (EA), which had less than 500 people, to create a spatial area layer that corresponded as closely as possible to the EA layer. The following criteria were used for the establishment of the SALs. EAs were merged if they fell within the same sub-place (a higher order geographic level); EAs were merged if they had the same geographical properties; an EA was merged if its population that resided there was less than 500 people; and lastly, the resulting SALs must have a population total of 500 or more [37].

Stratified sampling was chosen as it reduces sampling error and ensures a greater level of representation when compared to simple random sampling [38]. It also ensures more precise estimates, provided that there is homogeneity within strata and heterogeneity between strata [38]. A questionnaire will be administered and biological samples collected (two micro-containers of blood for dried blood spot (DBS), plasma specimens and self-collected vulvo-vaginal swab samples (VVSS) to test for HIV infection, HIV incidence, STIs as well as pregnancy respectively).

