**Measure risky sexual behaviour (e.g. number of [concurrent, lifetime, age-disparate] sexual partners, condom use, age of sexual debut), gender norms, intimate partner violence (including gender-based violence), and selected academic performance indicators (e.g. academic progress, school completion, assertive behaviour, participation in school and sport)**: The prevalence of risky sexual behaviour, gender norms and episodes of intimate partner violence (IPV) within the past year will be calculated with 95% CIs. IPV is assessed using behaviourally specific items developed by the World Health Organisation, and modified and used extensively in South Africa [47]. Five items ask about past experiences of physical violence from an intimate partner, whilst three items ask about sexual IPV in the previous year. Responses to each item are “never”, “once”, or “more than once”. A positive answer to any of the items leads to a woman being classified as having experienced IPV. Only women reporting having a boyfriend, husband, or having had sex with a man are asked these questions. Gender norms are measured using the gender equitable men (GEM) scale, this scale consists of 6 items relating to norms about male-female relationships and interactions. The scale asks respondents how much control their partners have over them in their relationships in relation to the clothes they wear, decisions made in the relationship and who they can spend time with outside of their relationship. Responses to each item are based on a Likert-type scale with responses ranging from strongly agree to strongly disagree. The scale items will be summed and a mean score calculated. Secondary analysis will be disaggregated by age, HIV and STI status and other socio-economic and academic indicators and exposure to DREAMS interventions.

**To measure the impact of economic empowerment, socio-economic status of their family, and selected parent/guardian/caregiver indicators have had on both the HIV incidence among AGYW and prevalence of GBV/IPV perpetrated against AGYW**: Composite scores will be created for AGYW using multiple correspondence analyses (MCA), taking the survey design and sampling weights into account.

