## Discussion

Ending the HIV/AIDS pandemic by 2030 requires the continual monitoring and evaluation of prevention programmes, with the aim of optimising efforts and ensuring the achievement of epidemic control. The monitoring of HIV prevalence is largely done through household surveys in SA [8]. However, key to determining the impact of initiatives targeting high-risk populations, including AGYW, is the collection of detailed data on the HIV response in a real world context, linking the scale-up of prevention efforts to changes in HIV incidence at a population level. This study will determine the impact DREAMS interventions have had on HIV incidence among AGYW in a ‘real world, non-trial setting’. This will be done by measuring HIV transmission within high-prevalence settings and within a high-risk population group, which will provide insights into the impact and efficacy of the DREAMS suite of prevention interventions.

The monitoring of temporal trends of HIV indicators will assist in improving and targeting prevention efforts and planning for health care delivery needs. This evaluation will be useful in implementing broader surveillance strategies and ensure they are supportive of the DREAMS interventions most effective to reduce risky sexual behaviour, increase knowledge of HIV status and subsequent uptake of ART, as well as reduce the prevalence of GBV.

This study has some limitations. Baseline incidence will need to be estimated. A longitudinal study design would have been preferred to establish baseline incidence prior to commencement of the DREAMS interventions and within the DREAMS targeted areas. Furthermore, a cross-sectional study cannot measure changes in behaviour and HIV incidence over time. This study would also not be able to determine the long-term impact of DREAMS being limited to information based on data gathered at a specific point in time. The study will only select participants from DREAMS targeted areas with the change in HIV infection rates estimated following the implementation of DREAMS programmes amongst AGYW through computation of the population’s attributable risk. As there is no non-DREAMS comparison arm in the study design, causal inferences regarding the relative contribution of DREAMS activities to measured reductions in key parameters is limited. The nature of the study did not allow for the establishment of a control group to assess the relative impact of the DREAMS interventions.

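### The abstract promises a DREAMS-attributable reduction in risk behaviours that one survey, with no behavioural baseline and no comparison arm, cannot measure

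*Protocol article*

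**What the plan says.** Five parts of the protocol article bear on this.

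- **Abstract, Background.** The aim covers two changes, both credited to the programme: "This study will assess the change in HIV incidence and reduction in risk associated behaviours that can be attributed to the DREAMS initiative".
- **Study design.** "This study is a single cross-sectional survey targeting 18,500 AGYW". There is no second round.
- **Study objectives.** The primary objective is a change, in incidence only: "Measure the change in HIV-1 incidence following implementation of the DREAMS suite of interventions". The behavioural objective is a level: "Measure risky sexual behaviour, specifically, the number of past year sexual partners, condom use, and age-disparate and concurrent partnering".
- **Analysis of secondary objectives.** Behaviour is analysed as a prevalence with 95% confidence intervals: "The prevalence of risky sexual behaviour, gender norms and episodes of intimate partner violence (IPV) within the past year will be calculated". Results are then broken down by age, HIV and STI status and "other socio-economic and academic indicators and exposure to DREAMS interventions". No comparison over time is described.
- **Discussion.** Among the limitations: "a cross-sectional study cannot measure changes in behaviour and HIV incidence over time". The same paragraph adds that, without a non-DREAMS arm, causal inference is limited.

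The Study aim section names external sources for a baseline (a national survey, an earlier longitudinal study and the provincial surveillance system in uMgungundlovu), but for HIV incidence only.

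**The concern.** A reduction needs two time points, or at least a credible earlier value. Attribution needs a comparator. For risk behaviours the article has neither, yet the abstract promises both.

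The practical risk lies in reporting. Anyone who writes results to match the abstract has only one DREAMS-related behavioural contrast to use: exposed against unexposed participants in the same survey. Presenting that difference as a reduction would misdescribe it. Exposure is self-reported, and it is not spread evenly over ages. The main Background section says that the age range of participants differs between activities: 10–14 year olds are left out of condom promotion, and PrEP goes to women aged 20–24 who engage in sex work. If the behaviours also vary with age, a crude exposed-versus-unexposed difference can appear with no programme effect at all.

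**Working it through.** No figure in the article needs reproducing. The sample size section deals with change in HIV incidence only and sizes no behavioural effect. The check is to set the statements side by side.

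| Needed for the abstract's claim | What the article provides for behaviours |
|---|---|
| A measurement after implementation | Yes: one survey, 2017/2018 |
| A measurement before implementation | None named; the external sources in Study aim are cited for incidence |
| A non-DREAMS comparator | None, as the Discussion states |
| An objective framed as change | No; the objective is to measure |
| An analysis of change | No; prevalence with 95% confidence intervals and a breakdown |

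Two other parts of the article might seem to fill the gap, and neither does. The population attributable risk mentioned in the Discussion refers to infection rates, not behaviour. The linear regression by exposure, under Analysis of secondary objectives, compares composite scores built from reported DREAMS exposure; it does not compare behaviours.

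**Illustration of the age problem (all inputs assumed, none from the article).** Let a behaviour have prevalence 10% at ages 15–19 and 30% at 20–24, the same for exposed and unexposed, so that there is no programme effect. Let *w* be the share aged 15–19. The crude prevalence is *w* × 10% + (1 − *w*) × 30%.

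- Exposed, *w* = 0.7: 0.7 × 10% + 0.3 × 30% = 7% + 9% = 16%.
- Unexposed, *w* = 0.5: 0.5 × 10% + 0.5 × 30% = 5% + 15% = 20%.
- Ratio: 16 / 20 = 0.80, an apparent 20% relative reduction.

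How far this moves depends on the assumed age mix:

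- Same mix in both groups: ratio 1.00.
- Mixes swapped (exposed 0.5, unexposed 0.7): 20 / 16 = 1.25, an apparent 25% increase.

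Within each age band the difference is zero by construction, so an age-adjusted contrast would return the correct answer in all three cases. The example shows the mechanism and that either sign is possible. It says nothing about the size to expect in this study.

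**The case against.** The strongest reply is that the operative text is consistent. Objective and analysis both treat behaviour as a level, no behavioural change analysis or sample size was built on the abstract sentence, and the Discussion openly states the limits on change and on causal inference. On this view a single sentence is out of line and nothing planned fails.

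Much of that stands. It is why this is a secondary matter of what may be claimed and not a fault in a planned calculation. But disclosure in the Discussion does not correct an aim stated in the abstract; the two cannot both hold.

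It may also be said that the analysis already lists age among the breakdown factors. It does, but alongside exposure; the text does not say that the exposure contrast is made within or adjusted for age. Covariate detail is often left to an analysis plan, so this is offered as an improvement to the contrast that replaces the claim, not as an omission.

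A reader might go further in four ways that the article does not support:

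- *The behavioural endpoint does not exist.* The behaviours are measured and analysed; what is missing is any basis for a reduction in them.
- *All the objectives are levels.* This is true of the behavioural objective. The primary objective is a change, in incidence.
- *School outcomes also lack a promised baseline.* The abstract promises a reduction in risk-associated behaviours only; academic milestones are a separate objective to measure.
- *The Discussion's closing summary repeats the error when it speaks of factors contributing to changes.* There the changes are in HIV incidence, so that sentence is not part of this point.

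**Conclusion.** Wrong as written, for a secondary aim. The abstract says the study will assess an attributable reduction in risk behaviours; one cross-sectional survey with no behavioural baseline and no non-DREAMS arm can give prevalences and associations only, as the Discussion itself implies. This rests on reading the sections against each other and on no statistical assumption.

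The size is in the conclusion, not in a number: the change in behaviour is not estimable from what the article describes. The 16% against 20% example rests on assumed inputs and is only an illustration of age confounding. The limitation quoted from the Discussion also mentions HIV incidence, but external baselines are named there, and this point does not reach the primary outcome.

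**What to change.** 1. Reword the abstract sentence so that, for behaviours, the study describes the prevalence of risk behaviours and their association with self-reported DREAMS exposure.
2. State that differences between exposed and unexposed participants will not be reported as a reduction or as attributable to DREAMS.
3. Under Analysis of secondary objectives, make the exposure contrast for behaviours age-adjusted, for example by a survey-weighted regression that includes age, in place of a crude breakdown. Age and exposure are already collected.

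The cost is a more modest claim and slightly more analysis; no data collection changes.

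A comparison with an earlier survey is optional. It would first require confirmation that items, ages and area are comparable, which the article does not show. On its incidence figures, the national survey is quoted for ages 15–24 at national level, and the provincial system covers uMgungundlovu with results for 15–19 and 20–24, whereas this study covers ages 12–24 in four districts.

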**Methods:**

Data will be collected from a household-based representative sample of AGYW (between the ages 12–24 years) in four high prevalence districts (more than 10% of the population have HIV in these districts) in South Africa in which DREAMS has been implemented. A stratified cluster-based sampling approach will be used to select eligible participants for a cross-sectional survey with 18,500, to be conducted over 2017/2018. A questionnaire will be administered containing questions on sexual risk behaviour, selected academic and developmental milestones, prevalence of gender based violence, whilst examining exposure to DREAMS programmes. Biological samples, including two micro-containers of blood and self-collected vulvovaginal swab samples, are collected in each survey to test for HIV infection, HIV incidence, sexually transmitted infections (STIs) and pregnancy. This study will measure trends in population level HIV incidence using the Limiting antigen (LAg) Avidity Enzyme Immuno-Assay (EIA) and monitor changes in HIV incidence.

**Discussion:**

Ending the HIV/AIDS pandemic by 2030 requires the continual monitoring and evaluation of prevention programmes, with the aim of optimising efforts and ensuring the achievement of epidemic control. This study will determine the impact DREAMS interventions have had on HIV incidence among AGYW in a ‘real world, non-trial setting’.

## Background

Adolescent girls and young women (AGYW) in sub-Saharan Africa remain the sub-population most susceptible to HIV infection [1]. In 2017, approximately 65% of all new HIV infections occurred in sub-Saharan Africa [2], with AGYW accounting for 74% of these infections, with more than 1000 HIV acquisitions amongst adolescents occurring daily [2, 3]. South Africa (SA) currently has the largest HIV epidemic in the world, with an estimated 7,520,000 people living with HIV (PLHIV) in 2018 [4]. A National surveillance study in 2017 estimated that 20.0% (95% CI 18.7–21.4) of South Africans fifteen years and older, were living with HIV [5] . In 2017, the prevalence amongst males was lower compared to females (4.7% versus 5.8% among those aged 15–19 years, and 4.8% versus 15.6% among those aged 20–24 years). The highest HIV-incidence (1.5%) is amongst South African females aged 15–24 years compared to 0.5% amongst young men their own age, translating into over 66,000 new infections amongst AGYW in South Africa (SA) in 2017 [5].

Several factors contribute to the observed increased rates of HIV acquisition amongst AGYW. Young women are biologically more susceptible to acquiring HIV than men. The risk of HIV transmission during unprotected vaginal intercourse is greater for women than men; and the risk for AGYW is further heightened because their vaginal tracts are immature and tissue tears occur more easily from sexual activity [6]. Furthermore, a study concluded that women with genital inflammation had an almost three-fold higher risk of HIV acquisition [7]. The risk of acquiring HIV also increases in the presence of sexually transmitted infections (STIs), with the majority of STIs occurring in young people under 25 years of age [8–10]. The estimated prevalence of STIs in South Africa among female clinic or community populations aged 15 to 24 years old was 20.6% for chlamydia, 8.9% for gonorrhoea, 20.0% for trichomoniasis, 53.7% for HSV-2, and 52.4% for bacterial vaginosis [11].

Compounding the prevalent biological factors, structural factors further facilitate HIV transmission amongst AGYW [12–14]. Many AGYW, enter into sexual relationships with older partners as a result of socioeconomic deprivation [15], with age-disparate relationships found to increase HIV-acquisition amongst AGYW [16–19]. Age disparate relationships increase AGYW’s susceptibility to HIV acquisition, because older men are more likely to be HIV positive [8, 20, 21], whilst these partnerships are also characterised by inconsistent condom use [22–24] and concurrent sexual partnering [25]. Relationships are also more likely to be transactional in nature [26], which has been demonstrated to also increase HIV acquisition [27]. In addition, AGYW are vulnerable to intimate partner violence (IPV) and dominant male partner behaviours, both of which increase their susceptibility to acquiring HIV [28].

In response to the high and sustained HIV-incidence among AGYW, interventions have been developed and implemented targeting this particular population cohort. The Determined, Resilient, Empowered, AIDS-free, Mentored and Safe (DREAMS) initiative is a comprehensive, multi-sectoral strategy introduced by the United States of America (U.S.) President’s Emergency Plan for AIDS Relief (PEPFAR) in 2014. DREAMS initiatives exist in 10 countries in sub-Saharan Africa: Kenya, Lesotho, Malawi, Mozambique, South Africa, Swaziland, Tanzania, Uganda, Zambia, and Zimbabwe. The initiative consists of evidence-based interventions, aimed at addressing the structural and behavioural drivers that increase AGYW risk of acquiring HIV, including poverty, gender inequality, gender-based violence (GBV), absence of parental and community support, and lack of education and vocational training [29]. The target of the DREAMS initiative is to reduce HIV incidence by 25% amongst AGYW in targeted high-prevalence areas by the end of the first year of implementation and by 40% at the end of the second year of implementation [30].

Each DREAMS country has identified context relevant interventions to include as part of an evidence-based approach to HIV prevention. In South Africa, DREAMS interventions are rolling out in five high HIV burden districts, namely: City of Johannesburg, Ekurhuleni, eThekwini, uMgungundlovu and uMkhanyakude. The DREAMS initiative is executed through existing U.S. government funded programme implementers including community, faith-based and non-governmental organizations, referred to as implementing partners, along with South African Government structures operating at the provincial, district, sub-district, metro, ward and village level. DREAMS aims to scale-up impactful and evidence-based interventions targeting AGYW, in an effort to bring the HIV/AIDS epidemic under control.

The DREAMS suite of interventions includes condom promotion and provision, HIV Counselling and Testing (HTS) and linkages to care, pre-exposure prophylaxis (PrEP) (targeting sex workers specifically), GBV prevention as well as post-violence care and support; linkage to sexual reproductive health (SRH) services, comprehensive sexuality education and social asset building. DREAMS initiatives aim to strengthen school-based HIV and GBV prevention efforts, together with strengthening community mobilisation and norm change efforts through parenting and caregiver programmes, social protection initiatives and interventions specifically targeting male sex partners. The age range of participating AGYW varies across these different activities. For example, 10–14 year olds are not included in condom promotion activities, while PrEP is provided to young women aged 20–24 years who engage in sex work [31]. Whilst younger girls together with boys and men are targeted by some of the aforementioned interventions, this study focuses on females aged between 12 and 24 years of age. The evaluation will provide data on the impact of the DREAMS interventions and will inform future development and potential expansion of these interventions targeting adolescent girls and young women.

